## 2. Materials and Methods

### 2.1. Study Design

This randomised, two-period, crossover trial investigates the effects of RT in comparison to OT on upper extremity function in individuals with intermediate cSCI. The study protocol follows the Standard Protocol Items: Recommendations for Interventional Trials 2013 Statement [15] (Supplement S1). This publication is based on version 1.2 of the study protocol, dated 20 August 2025. Recruitment of participants has been ongoing since 10 June 2025, and data collection is estimated to end in June 2028. The study is conducted at the Swiss Paraplegic Centre (SPC) located in Nottwil, Switzerland.

Participants are enrolled between day 16 and day 81 post-injury (Figure 1). The study takes 15 weeks, of which 12 weeks are devoted to therapy interventions and 3 weeks are devoted to assessments. In case the participants complete the intermediate assessment t_2_ before day 150 after injury, a follow-up assessment t_3_ of one week will take place around four weeks after t_2_, in line with the European Multicentre Study about Spinal Cord Injury (EMSCI) study timeline. With this, the study would take 20 weeks in total. The therapy interventions consist of RT as the experimental intervention and conventional OT as the control intervention. Both therapy interventions, RT and OT, are executed unilaterally and are additional to the clinical routine therapy scheme. Whereas the upper extremity included in the study is chosen by the participants together with their therapists, the sequence of the intervention blocks is randomly assigned. Each intervention block comprises 3 × 30 min training sessions per week for 6 weeks.

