### 2.2. Participants and Randomisation

The study population comprises individuals with cSCI who have upper extremity impairments and are in the intermediate stage of recovery (2 weeks to 6 months post-injury). Eligible participants include adults (≥18 years) with traumatic or non-traumatic cSCI with a neurological level of injury (NLI) between C1 and T1 and classified as AIS grades A–D [18]. Detailed inclusion and exclusion criteria are provided in Table 1.

In total, 40 participants will be randomised to one of the two intervention sequences. Participants will be randomised 1:1 using a permuted block design with a block size of four, stratified by their predicted recovery profile [16]. It has been shown that upper extremity function at six months after onset of cSCI can be predicted using two specific upper extremity muscles. The two predictors are the Flexor Digitorum Profundus muscle of the International Standards for the Neurological Classification of Spinal Cord Injury (ISNCSCI-FDP) and the Musculus deltoideus pars acromialis of GRASSP (GRASSP-Delto) [16]. Both predictors will be assessed between day 16 and day 40 after onset of cSCI to derive the corresponding stratum for stratified randomisation. This will ensure well-balanced intervention sequences in terms of the predicted recovery potential and may facilitate the identification of participant subgroups that show particularly strong or weak responses to one of the interventions.

The stratified permuted block randomisation is implemented using the web-based data capture and management system secuTrial (iAS, Berlin, Germany; see Data management and safety provisions). The randomisation algorithm was configured by the data manager of the clinical trial unit (CTU) of Swiss Paraplegic Research, ensuring that the allocation sequence remains concealed from the investigators. Allocation is only revealed to qualified members of the study team after an enrolled participant’s randomisation is triggered within secuTrial. Therefore, concealment of allocation will be ensured.

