### 2.7. Statistical Analysis Plan

This exploratory randomised crossover trial is designed to estimate the pattern and magnitude of intervention effects on upper extremity function in individuals with cSCI. While primarily exploratory, the design allows for formal testing of superiority if a sufficiently strong intervention effect is observed.

In total, the study will randomise 40 participants to one of two intervention sequences. The crossover design enables paired comparison of intervention effects. Hence, a sample size of 34 evaluable participants will allow detection of a minimal clinically important difference (MCID) of three points in the primary outcome GRASSP-QtG with a power of 80% and a significance level of 5% (two-sided), as long as the corresponding within-group standard deviation does not exceed six points (corresponding to a medium effect size). Based on the number of patients with cSCI in previous years [11] and accounting for a 15% attrition rate, the study aims for a recruitment duration of two and a half years after first patient in to reach the calculated sample size of 40 participants.

Descriptive statistics will summarise the baseline characteristics of the study participants. Even though the SCI population is characterised by a predominance of males (~70%) [27,28], the neurological and functional recovery profiles have been found to be comparable between genders [29]. Therefore, no gender-specific stratification is planned. However, gender balance will be ensured within the study team for data collection, analysis, and authorship.

The primary and secondary outcomes will be analysed as changes within each period using linear mixed models. A two-sided significance level of α = 0.05 will be used for superiority testing. The model will include the baseline value measured at the start of the study, TREATMENT as a categorical variable with two levels (RT and OT), and PERIOD as a categorical variable with two levels (first and second) to assess the differences in changes in GRASSP-QtG between timepoints (i.e., t_1_–t_0_ and t_2_–t_1_). In addition, subject- and stratum-specific random intercepts will account for within-subject and within-stratum correlation across timepoints. To assess potential carryover effects, a second model will additionally include the TREATMENT × PERIOD interaction and SEQUENCE as a categorical variable with two levels (RT-OT and OT-RT). No interim analyses are planned for the main outcomes.

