Applying the interventions in a crossover study design has multiple advantages. First, every participant receives both the experimental and control interventions, eliminating ethical concerns about the selection of the comparator or unequal intervention allocation. Regardless of sequence (RT followed by OT or vice versa), participants engage in an intensive 12-week unilateral training program in addition to clinical routine therapy scheme, potentially enhancing functional recovery of the respective upper extremity. Additionally, participants decide together with their therapist which upper extremity to include in the study. This allows them to prioritise either the more severely impaired side to maximise recovery potential or the less impaired side to promote functional independence.

Moreover, the crossover design enables a within-participant comparison. This reduces interindividual variability and the total sample size required to detect meaningful effects. This design also permits the evaluation of sequence effects, providing information if a certain intervention sequence is more favourable compared to the other. Because only one upper extremity is randomised while both arms continue clinical routine therapy, the design allows comparison between the trained and untrained upper extremity. It yields information about the overall benefit of the additional intensive therapies compared to clinical routine therapies as well as the effectiveness of RT compared to OT. These exploratory tests can help to define new hypotheses for future research.

Despite its strength, the crossover design cannot eliminate the carry-over effects. The carry-over effects are taken into account by focusing the analysis on the improvements within each intervention block rather than the absolute results at each assessment timepoint. Consequently, improvements during the first intervention block could influence outcomes in the second. However, a specific wash-out period is not feasible and ethically inappropriate as the reacquired functions are unlikely to decline during primary rehabilitation.

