Furthermore, time during primary rehabilitation is a strong determinant of motor recovery and may therefore influence observed improvements during the first compared to the second intervention period. By including PERIOD and the baseline measurement in the linear mixed model, we account for overall time-related recovery effects and thereby reduce confounding by the underlying recovery trajectory when estimating the treatment effect. However, potential carryover effects will be explicitly assessed and considered in the interpretation of the results.

Additionally, whereas only one arm will be randomised to one of the two sequences of intervention blocks, both arms continue with the clinical routine therapy. Although the clinical routine therapy could affect the study objectives, it would not be ethical to restrict the clinical routine therapy during primary rehabilitation after cSCI. However, the influence on the primary objective is reduced by the within-subject comparison due to the crossover design, provided that the concomitant therapy does not differ systematically between the blocks.

Finally, by having stratified randomisation in the crossover design, new hypotheses can be generated from exploratory subgroup analysis. With this, more information about possible individualisation of therapy schedules dependent on the patients’ predicted recovery profiles can be provided in the future.

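### The carry-over model contains the same contrast twice: in a two-period, two-sequence crossover TREATMENT × PERIOD and SEQUENCE cannot both be estimated, and the one contrast that remains does not isolate carry-over

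*Protocol article*

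**What the plan says.** Section 2.1 of the protocol article describes the design: "This randomised, two-period, crossover trial investigates the effects of RT in comparison to OT". Section 2.2 adds: "In total, 40 participants will be randomised to one of the two intervention sequences". Under section 2.7 the outcomes are "analysed as changes within each period using linear mixed models", which gives each participant two responses, t1 minus t0 and t2 minus t1.

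The primary model has the study baseline, TREATMENT (two levels) and PERIOD (two levels) as fixed effects, with random intercepts for subject and stratum. For carry-over, the same section says that "a second model will additionally include the TREATMENT × PERIOD interaction and SEQUENCE as a categorical variable with two levels". Both terms therefore enter one model, on top of those already there.

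Section 3 relies on this in two places. On the merits of the design it says: "This design also permits the evaluation of sequence effects, providing information if a certain intervention sequence is more favourable compared to the other". On its limits it says that "potential carryover effects will be explicitly assessed and considered in the interpretation of the results". The same section concedes that no wash-out is possible and that gains in the first block could influence the second.

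**The concern.** In this design, knowing the treatment and the period tells you the sequence. A model with an intercept, TREATMENT, PERIOD, their interaction and SEQUENCE asks five parameters of four sequence-by-period cell means. One parameter has nothing left to estimate it.

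Two things are at stake. First, the prespecified carry-over analysis cannot be run as written. What gets reported depends on how the software or the analyst resolves the redundancy. Second, the text reads as though carry-over has an assessment of its own alongside the sequence comparison, when there is a single degree of freedom for both. This matters more than usual here because there is no wash-out, recovery is under way throughout, and this is the only carry-over check that the article states.

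**Working it through.** **1. The plan's own figure.** Section 2.7 gives 34 evaluable participants for a 3-point difference, SD 6, 80% power and two-sided 5%. A paired t-test with d = 3/6 = 0.5 needs n = 33.4, so 34, and power at 34 is 0.808. Attrition of 15% gives 34/0.85 = 40. The sample size reproduces, and the point below does not depend on it.

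**2. The alias.** Code T = 1 for RT, P = 1 for the second period and S = 1 for the sequence OT-RT.

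| Sequence | Period | T | P | S | T×P | -0.5 + 0.5T + 0.5P + 0.5S |
|---|---|---|---|---|---|---|
| RT-OT | 1 | 1 | 0 | 0 | 0 | 0 |
| RT-OT | 2 | 0 | 1 | 0 | 0 | 0 |
| OT-RT | 1 | 0 | 0 | 1 | 0 | 0 |
| OT-RT | 2 | 1 | 1 | 1 | 1 | 1 |

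The last two columns agree in every row, so T×P is an exact linear combination of the intercept, T, P and S.

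**3. Rank of the fixed-effects matrix** (34 participants, two periods):

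| Model | Columns | Rank |
|---|---|---|
| T + P + baseline (primary) | 4 | 4 |
| T + P + T×P | 4 | 4 |
| T + P + S | 4 | 4 |
| T + P + T×P + S | 5 | 4 |
| T + P + T×P + S + baseline | 6 | 5 |

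Baseline is constant within a participant and does not break the alias. Random intercepts do not either, since they leave the fixed-effects matrix unchanged. Removing some records left the rank at 5 of 6.

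**4. What software does with it** (one simulated data set, subject intercept only). With both terms, nlme::lme stopped with a singularity error. lme4::lmer reported rank deficiency, dropped the interaction and fitted the rest with SEQUENCE kept.

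**5. Either term alone gives the same model.** On those data, with baseline included, both versions had log-likelihood -176.84 and p = 0.218 for the extra term. The interaction coefficient (-2.080) was twice the SEQUENCE coefficient (-1.040). With complete data this is expected. SEQUENCE is the difference per period, and twice that is the difference in t2 minus t0.

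The TREATMENT coefficient does differ between the versions. It was 0.355 with SEQUENCE kept (the period-adjusted effect) and 1.395 with the interaction kept under 0/1 coding (the first-period difference alone). The gap, 1.395 - 0.355 = 1.040, is the size of the SEQUENCE coefficient.

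**6. Precision of the remaining contrast.** The article gives no SD for t2 minus t0. Assume that the SD of 6 is that of the paired difference, that the two change scores have equal variance and correlation ρ, that there are 17 participants per sequence, and that there is no covariate adjustment. Then

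SD(t2 - t0) = 6 × √[(1 + ρ)/(1 - ρ)].

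A two-sample t-test with 32 degrees of freedom detects 0.991 × SD at 80% power.

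| ρ | SD of t2 - t0 | Detectable at 80% | Power for 3 points |
|---|---|---|---|
| -0.5 | 3.5 | 3.4 | 69% |
| -0.3 | 4.4 | 4.4 | 49% |
| 0 | 6.0 | 5.9 | 29% |
| +0.5 | 10.4 | 10.3 | 13% |

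Negative values of ρ have to be allowed, because the two changes share t1 with opposite signs and the scale stops at 30 points.

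**The case against.** The strongest reply is that little of practical weight is damaged. The treatment effect comes from the primary model, which has full rank. The second model is supplementary, in a trial that calls itself exploratory. In lme4 the model as written reduces to the version with SEQUENCE alone, which is the sensible one, and lmer says that it has dropped a column. All of this stands, and it limits the point to a wording correction.

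A reader might infer four stronger things, none of which the article supports:

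- **That the model cannot be fitted at all.** Some software fits it after removing a column. What cannot be had is two separate coefficients.
- **That sequence effects cannot be evaluated.** The sentence in section 3 asks which sequence is more favourable. The comparison of t2 minus t0 between the randomised sequences answers that, whatever the mechanism. The sentence is not wrong. It only fails to say that this is the same contrast as the carry-over check.
- **That the reported treatment effect is unstable.** It would change only if an analyst removed SEQUENCE instead and then took TREATMENT from a model not meant to supply it.
- **That a non-significant result will be taken to mean no carry-over.** The article sets no such rule and openly says that carry-over cannot be eliminated.

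Low power is also not a fixed figure. It depends on a correlation that the article does not give, and adjustment for baseline and stratum could help.

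**Conclusion.** The point holds for the second model in section 2.7. It names two terms that are one contrast, which is a matter of algebra and needs no assumption (rank 4 of 5, or 5 of 6 with baseline). Only one coefficient is estimable. It mixes carry-over, treatment-by-period interaction and chance difference between the sequence groups, so the promise in section 3 of an explicit carry-over assessment is too strong.

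The statement on precision does rest on assumptions: SD 6 for the paired difference, equal variances, ρ from -0.5 to +0.5, 17 per sequence and no covariate adjustment. Across that range the detectable difference runs from about 3.4 to 10.3 points, and power for 3 points from about 69% to 13%, below 80% throughout. The primary model, its test and the sample size are unaffected.

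**What to change.** In section 2.7, remove TREATMENT × PERIOD from the second model and keep SEQUENCE as its single added contrast, so that TREATMENT remains the period-adjusted effect. State that the SEQUENCE coefficient is half the difference in t2 minus t0 between sequences (with complete data), so that the scale of the report is clear. Report the estimate with a 95% CI, labelled as not separating carry-over, treatment-by-period and sequence effects, and say that a non-significant result is not evidence of no carry-over.

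In section 3, add to the two sentences quoted above that the sequence comparison and the carry-over assessment are this same contrast, and temper the claim of explicit assessment accordingly.

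The cost is a few sentences. No data, visit or sample-size change is needed. Data collection is expected to run to June 2028, so the correction can be made well before analysis.

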### 2.8. Dissemination Policy

The results of this study will be published in appropriate scientific journals and presented at relevant conferences. The CONSORT (extension to randomised crossover trials) guidelines as well as the flow diagram (Supplement S3) for publishing study results [30,31] will be followed. If sex- or gender-specific effects are observed, they will be published in the final study report. The Sponsor will enter and publish a summary of the results of the clinical investigation in a publicly recognised register immediately after submitting the final report. The investigator will provide each participant with the lay summary of the results of the clinical investigation at the end of the study.

## 3. Strengths and Limitations

Despite the limited evidence for RT in upper extremity rehabilitation following cSCI, it is frequently used in clinical practice. Therefore, this randomised crossover study was designed to systematically probe the effects of RT compared to conventional OT on upper extremity function in individuals with intermediate cSCI.

For developing this randomised crossover study design, the results and specific limitations of previous studies were considered. The ArmeoSpring device was selected for the experimental intervention due to its established advantages of widespread clinical use [11] and the significant functional improvements previously observed in a subgroup with residual hand function [12]. In contrast to earlier RCTs [7,8], the current study requires stricter inclusion criteria regarding the enrolment timepoint (16 < t_0_ < 81 days post-injury). With this, the majority of motor recovery can be targeted, which occurs within the first 6–9 months [10]. Whereas Bertels, et al. [32] concluded in their review that a minimum duration of 8 weeks will lead to improvements in function and activity level, Zariffa, et al. [12] showed that planned sessions of 1 h 3–5 times a week were not feasible. Additionally, considering that the first additional RT or OT intervention block already starts around 3 months post-injury, the current study comprises 3 × 30 min training sessions per week for 6 weeks per intervention block. These fewer and shorter therapy durations were determined according to reported therapy sessions in the literature varying between 30 and 60 min 3–5 times per week for 4–6 weeks [7,8,12] and are in line with existing clinical practices described by Kuchen, et al. [11].

Applying the interventions in a crossover study design has multiple advantages. First, every participant receives both the experimental and control interventions, eliminating ethical concerns about the selection of the comparator or unequal intervention allocation. Regardless of sequence (RT followed by OT or vice versa), participants engage in an intensive 12-week unilateral training program in addition to clinical routine therapy scheme, potentially enhancing functional recovery of the respective upper extremity. Additionally, participants decide together with their therapist which upper extremity to include in the study. This allows them to prioritise either the more severely impaired side to maximise recovery potential or the less impaired side to promote functional independence.

Moreover, the crossover design enables a within-participant comparison. This reduces interindividual variability and the total sample size required to detect meaningful effects. This design also permits the evaluation of sequence effects, providing information if a certain intervention sequence is more favourable compared to the other. Because only one upper extremity is randomised while both arms continue clinical routine therapy, the design allows comparison between the trained and untrained upper extremity. It yields information about the overall benefit of the additional intensive therapies compared to clinical routine therapies as well as the effectiveness of RT compared to OT. These exploratory tests can help to define new hypotheses for future research.

Despite its strength, the crossover design cannot eliminate the carry-over effects. The carry-over effects are taken into account by focusing the analysis on the improvements within each intervention block rather than the absolute results at each assessment timepoint. Consequently, improvements during the first intervention block could influence outcomes in the second. However, a specific wash-out period is not feasible and ethically inappropriate as the reacquired functions are unlikely to decline during primary rehabilitation.

Furthermore, time during primary rehabilitation is a strong determinant of motor recovery and may therefore influence observed improvements during the first compared to the second intervention period. By including PERIOD and the baseline measurement in the linear mixed model, we account for overall time-related recovery effects and thereby reduce confounding by the underlying recovery trajectory when estimating the treatment effect. However, potential carryover effects will be explicitly assessed and considered in the interpretation of the results.

Additionally, whereas only one arm will be randomised to one of the two sequences of intervention blocks, both arms continue with the clinical routine therapy. Although the clinical routine therapy could affect the study objectives, it would not be ethical to restrict the clinical routine therapy during primary rehabilitation after cSCI. However, the influence on the primary objective is reduced by the within-subject comparison due to the crossover design, provided that the concomitant therapy does not differ systematically between the blocks.

Finally, by having stratified randomisation in the crossover design, new hypotheses can be generated from exploratory subgroup analysis. With this, more information about possible individualisation of therapy schedules dependent on the patients’ predicted recovery profiles can be provided in the future.

